#### *Efficacy assessment tools*

1. MCID calculation [11]: The MCID value will be calculated using the SEM method and following the steps outlined below:

1.a. Calculation of M (M_0_ and M_1_) (Figure 2):

**Figure 2 F2:**
[figure not shown]
**Calculation of the M value.** SAQ, Seattle Assessment Questionnaire.

1.a.i. Find patients receiving treatment A (or treatment B) whose self-reported Likert scores are within the range of +2 to +3.

1.a.ii. Collect the corresponding SAQ score of these patients, use X_1_ to refer to it and calculate the mean value $X{\left(—\right)}_{1}$.

1.a.iii. Find patients receiving Treatment A (or Treatment B) whose self-reported Likert scores are within the range of 0 to +1.

1.a.iv. Collect the SAQ scores of these patients, use X_0_ to refer to it and calculate the mean value X_0_

1.a.v. $M_{0}=X_{0}-X{\left(—\right)}_{0}$

1.a.vi. $M_{1}=X_{1}-X{\left(—\right)}_{1}$

2. Calculation of SEM (SEM_0_ and SEM_1_) [7,12,13].

$$\mathrm{SEMO}=\sqrt{\sum M0^{2}/\left(n-1\right)}\times \sqrt{1-r}$$

$$\mathrm{SEM}1=\sqrt{\sum M1^{2}/\left(n-1\right)}\times \sqrt{1-r}$$

n:sample size; r:the reliability coefficient of SAQ

3. Calculation of MCID We will calculate the MCIDs for treatment A (referred to as MCID1) and treatment B (referred to as MCID2) during the first treatment period and for treatment A (referred to as MCID3) and treatment B (referred to as MCID4) during the crossover period.

MCID, Minimal clinically important difference; SEM, Standard error of measurement.

$$\mathrm{MCID}\;=\;\sqrt{\mathrm{SEM}O^{2}+\mathrm{SEM}1^{2}}$$

4. Individualized efficacy evaluation upon the first round of treatment: Treatment interventions will be defined as either effective or ineffective by comparison of the patient’s personal SAQ score with the calculated MCID value.

4.a. Treatment A will be defined as effective if a patient receiving it has a SAQ score greater than the MCID1 score.

4.b. Treatment B will be defined as effective if a patient receiving it has a SAQ score greater than the MCID2 score.

4.c. A treatment will be adjudged ineffective if a patient receiving it reports a SAQ score lower than the corresponding MCID value (MCID1 or MCID2).

5. Individualized efficacy evaluation upon crossover of treatment: Because of the complexity of the study design, all the patients will be categorized into four groups by using the following assessment tools:

5.a. Group 1: Both treatments A and B are effective for patients in this group:

5.a.i. For patients who first receive treatment A and then treatment B, the first SAQ score > MCID1 and the second SAQ score > MCID4

5.a.ii. For patients who first receive treatment B and then treatment A, the first SAQ score > MCID2 and the second SAQ score > MCID3

5.b. Group 2: Treatment A is effective and treatment B is ineffective for patients in this group:

5.b.i. For patients who first receive treatment A and then treatment B, the first SAQ score > MCID1 and the second SAQ score < MCID4

5.b.ii. For patients who first receive treatment B and then treatment A, the first SAQ score > MCID2 and the second SAQ score < MCID3.

5.c. Group 3: Treatment B is effective and treatment A is ineffective for patients in this group:

5.c.i. For patients who first receive treatment A and then treatment B, the first SAQ score < MCID1 and the second SAQ score > MCID4

5.c.ii. For patients who first receive treatment B and then treatment A, the first SAQ score < MCID2 and the second SAQ score > MCID3

5.d. Group 4: Both treatments A and B are ineffective for patients in this group:

5.d.i. For patients who first receive treatment A and then treatment B, the first SAQ score < MCID1 and the second SAQ score < MCID4

5.d.ii. For patients who first receive treatment B and then treatment A, the first SAQ score < MCID2 and the second SAQ score < MCID3

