### Minimal clinically important differences and patient-reported outcome measurements

Minimal clinically important differences (MCIDs) are self-perceived scores that signify clinically significant improvements in PROs that can be used to identify the minimal changes in a specific aspect of a patient’s health [7], and it is believed to reflect the smallest change in the PRO evaluations of a clinical intervention that is meaningful to the patient.

Distribution-based methods for the determination of MCIDs have been widely used and can be subdivided into the effect size (ES) and the standard error of measurement (SEM). The latter measurement is particularly recommended for its relative independence from sample source and stability across different studies [8,9]. In our present study, changes in PROs will be calculated using the SEM, which will represent patients’ self-reported improvements in symptoms or health-related function.

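### Each drug is judged against its own MCID, built from that arm's own scatter, so the same SAQ change can count as effective on one drug and ineffective on the other

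*Protocol article*

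**What the plan says.** All references are to the protocol article, under *Efficacy assessment tools* unless another section is named.

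- **Data used.** Steps 1.a.i and 1.a.iii select patients within one treatment by Likert band. The upper band is set by "Find patients receiving treatment A (or treatment B) whose self-reported Likert scores are within the range of +2 to +3". The lower band is set by "Find patients receiving Treatment A (or Treatment B) whose self-reported Likert scores are within the range of 0 to +1". M is each patient's SAQ score minus the mean of that band.
- **Formula.** SEM is the root of ΣM²/(n−1), times √(1−r), for each band. MCID is √(SEM0² + SEM1²). The legend is "n:sample size; r:the reliability coefficient of SAQ". No value of r is given.
- **Four thresholds.** Step 3 sets the first pair: "We will calculate the MCIDs for treatment A (referred to as MCID1) and treatment B (referred to as MCID2) during the first treatment period". Its second pair repeats this after the switch: "for treatment A (referred to as MCID3) and treatment B (referred to as MCID4) during the crossover period".
- **Use.** Step 4 gives the rule for QSYQ as "Treatment A will be defined as effective if a patient receiving it has a SAQ score greater than the MCID1 score". Its counterpart for TXL is "Treatment B will be defined as effective if a patient receiving it has a SAQ score greater than the MCID2 score". Step 5 combines the two periods into Groups 1 to 4, using MCID1 and MCID4 for the A-then-B sequence and MCID2 and MCID3 for B-then-A. The groups fill Tables 1 and 2 and the correspondence analysis.
- **Reason for the SEM.** The background section on MCIDs says of it: "The latter measurement is particularly recommended for its relative independence from sample source and stability across different studies".

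No common or pooled MCID appears anywhere in the article.

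**The concern.** The band means cancel out of M, so each threshold reflects only the within-band scatter of the arm being judged, and r. The arm with the more variable response gets the higher bar. The background section treats the MCID as the smallest change that matters to a patient, which should not depend on the drug the patient was assigned. Recomputing it by arm and by period also gives up the independence from the sample that is offered as the reason for choosing the SEM. The same drug can even face two different bars, MCID1 and MCID3 for A, or MCID2 and MCID4 for B.

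The stated aim is to compare the two drugs and find the best indications for each. If the bars differ, a difference in effective rates can come from the bars rather than the drugs.

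**Working it through.** **Nothing to reproduce.** The article gives no MCID, no r, no within-band SD and no band counts. What follows illustrates the rule and does not predict the result.

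**Inputs.**
- Change in SAQ: normal, SD 2.5, identical on both drugs. The 2.5 is borrowed from the pilot figure of 2 ± 2.5 in *Sample size calculation*.
- Mean change: 1 to 3 (assumed).
- Within-band SD: 2 on A and 3 on B, equal in both Likert bands (assumed).
- r: 0.7 to 0.9 (assumed).
- The SAQ score in steps 4 and 5 is read as a change (assumed; see the objection).

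**Formulas.** With equal SD in the two bands, MCID = SD_band × √(2(1−r)). Effective rate = Φ((mean − MCID)/2.5).

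**Step 1: same change distribution, separate thresholds, mean change 2.**

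| r | MCID A | MCID B | Rate A | Rate B | Gap (points) |
|---|---|---|---|---|---|
| 0.7 | 1.55 | 2.32 | 57.2% | 44.8% | 12.3 |
| 0.8 | 1.26 | 1.90 | 61.6% | 51.6% | 9.9 |
| 0.9 | 0.89 | 1.34 | 67.1% | 60.4% | 6.7 |

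Gaps are taken before rounding. Over mean change 1 to 3 they run from 5.4 to 12.3 points. At r = 0.8, a change of 1.5 is effective on A (above 1.26) and ineffective on B (below 1.90). With within-band SDs of 2 and 2.5 the gaps run from 2.6 to 6.1 points.

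**Step 2: one common threshold.** With the same distribution on both drugs the gap is zero. For example, an MCID of 1.58 (SD 2.5, r = 0.8, mean 2) gives 56.7% on both.

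**Step 3: equal true spread.** The expected gap is zero under the plan as well, but the thresholds are estimated. In 20,000 simulated pairs of identical arms (mean change 2, SD 2.5), with 10 to 20 patients per band assumed, the larger MCID was typically 1.12 to 1.18 times the smaller. The absolute rate gap had a median of 1.8 to 4.9 points and a 95th percentile of 5.4 to 14.0, in either direction.

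**Step 4: where it enters Groups 2 and 3.** Let pA and pB be the effective rates, with no period effect and with thresholds equal across periods.
- A-then-B: Group 2 minus Group 3 = P(A effective, B not) − P(B effective, A not) = pA − pB.
- B-then-A: 5.b.ii assigns Group 2 when the first score (on B) exceeds MCID2 and the second (on A) is below MCID3. That is B effective and A not, the reverse of the group's label; 5.c.ii mirrors it. The difference is pB − pA.
- Averaged at 1:1, with the r = 0.8 rates: (9.9 − 9.9)/2 = 0. With the labels corrected: (9.9 + 9.9)/2 = 9.9 points.

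**Step 5: what a common threshold cannot do.** Let the whole change distribution differ in spread (SD 2 on A, 3 on B, r = 0.8), with the same SDs used in the bands. The pooled MCID is √((4+9)/2) × √0.4 = 1.61.
- Mean change 2: separate thresholds give 64.3% against 51.4%, a gap of about 13 points. The pooled one gives 57.7% against 55.1%, about 2.5. Roughly 10 points are due to the thresholds.
- Mean change 0: separate thresholds give no gap. The pooled one gives 8.5 points, in favour of B.

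**The case against.** **The size is assumed.** The article gives one SD, 2.5, and no sign that the arms differ in spread. With equal spread the expected gap is zero. A within-band SD of 3 beside an overall SD of 2.5 also requires the other Likert bands to be tighter. This stands: the 5 to 12 points are conditional.

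**The group comparison.** A reader might infer that Group 2 versus Group 3 is biased as the rules are written. They do not support that: with 5.b.ii and 5.c.ii reversed, an A/B threshold bias cancels at 1:1. The bias appears there once the labels are put right, as they must be for the tables to mean what they say. The separate A and B rates in step 4 are affected either way.

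**Pooling as a complete cure.** A reader might also infer that a common threshold always gives equal rates to drugs with equal mean benefit. Step 5 of the working shows that it does not when the spreads truly differ. The case for it is that both drugs face the same bar.

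**Score or change.** Steps 4 and 5 speak of a SAQ score, and the section on measurement tools lists collection only after each treatment period. If a raw score far above any MCID were meant, nearly every patient would be effective and unequal bars would matter little. The sample size section works with changes and the background defines the MCID as a change, so change is the sensible reading. It remains an assumption.

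**The legend for n.** One could read n as the whole arm while the sum covers one band. That is only an ambiguity: a sum of squares over n−1 naturally takes the number summed, and the working uses that reading.

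**Exploratory purpose.** The discussion calls the study exploratory, and no hypothesis test is attached to the groups. This limits the severity but does not remove the point, since the aim is still to compare the drugs.

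**Conclusion.** The point holds as a flaw in a stated rule. The plan fixes four MCIDs by treatment and period, each from that arm's own post-treatment within-band scatter, and judges each drug against its own. An identical SAQ change can therefore be classed differently on the two drugs, and the article's reason for using the SEM is undercut.

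With SAQ score read as change and the same change distribution on both drugs, the distortion is about 5 to 12 points for within-band SDs of 2 and 3, and about 3 to 6 points for 2 and 2.5. With equal true spread it reduces to estimation noise. It falls on the separate A and B rates now, and on Group 2 versus Group 3 once the labels are corrected. The reading of the text is firm; the size is illustrative. This should be changed, but it does not by itself invalidate an exploratory trial.

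**What to change.** 1. In step 3, replace MCID1 to MCID4 with one MCID for change in SAQ. Form the two Likert bands from all patients, pooled over both treatments and both periods, and calculate the value blind to treatment, before unblinding.
2. Use that single value throughout steps 4 and 5, and say there that the quantity compared is the change in SAQ.
3. Correct 5.b.ii and 5.c.ii so that Group 2 means A effective and B ineffective in both sequences, and Group 3 the reverse. Items 1 and 3 belong together: a common threshold alone would leave the groups mislabelled.
4. State that n in each SEM is the number of observations in that Likert band.

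The cost is protocol wording and somewhat simpler code, with no extra patients. The pooled threshold should also be more precise, though by less than the count of observations suggests, because each patient contributes to both periods. It is still derived from data after randomisation, but no longer from the arm being judged. Rate differences that come from truly unequal spread will remain, so the mean and SD of the SAQ change should be reported for each drug beside the effective rates.

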#### *Assignment of interventions*

In this study, we adopt a crossover design which involves three key phases: a 4-week treatment period, a 10-day washout period and the crossover of treatment for another 4 weeks:

1. The first treatment period (4 weeks): A total of 160 participants will be randomly assigned to receive treatment A or treatment B for 4 weeks.

1.a. Treatment A: QSYQ dripping pills + TXL placebo + routine medication

1.b. Treatment B: TXL capsules + QSYQ placebo + routine medication

2. Washout phase (10 days): After the first round of treatment, patients in both groups will receive QSYQ placebo and TXL placebo plus routine medication for 10 days.

3. Crossover of treatments (4 weeks): In this stage, patients formerly assigned to treatment A will be switched to treatment B and those assigned to treatment B will be switched to treatment A.

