#### *Routine medication*

Routine medications will include aspirin, angiotensin-converting enzyme inhibitors or angiotensin receptor blockers, β-receptor blockers, statins and nitrates.

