### Measurement tools and time of data capture

The SAQ and 15-point Likert scale scores will be used to collect PROs immediately following the first treatment period and the crossover treatment period. The minimal clinically important differences (MCIDs) of the SAQ and the Likert scale scores at these two time points will be calculated for efficacy evaluation and comparison.

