### Correspondence analysis

Correspondence analysis (CA) is a statistical technique designed to demonstrate or summarize a set of data in two-dimensional graphical form, typically a biplot, which can help in the detection of the structural relationships among the variables contained in the rows and columns of a contingency table. In this study, SPSS version 16.0 software (SPSS Inc, Chicago, IL, USA) will be used to perform CA of the data in Tables 1 and 2. Statistical analysis will follow the steps listed below:

1. Specify the value of dimensions.

2. For both tables, the number of dimensions will be set at two.

3. Production of a CA plot.

The biplot is a matrix of joint plots of the row and column points. In the biplot, types of symptom combinations and different outcome groups are shown as points. The abscissa value is determined by the score of the first dimension of symptom combinations and outcome groups. The ordinate value is the score of the second dimension of symptom combinations and outcome groups.

4. Calculation of “D (A–B)” refers to the relative distance between point A and point B in the biplot. “a1” and “b1” refer to the abscissa values of point A and point B. “a2” and “b2” refer to the ordinate values of point A and point B.

5. The relative distance between points displayed in the CA plot will be summarized in a table. As prespecified, the pair of symptom combinations and outcome types with the nearest relative distance will signify the most significant correlation. The characteristic indications for which the patent drug is most effective will be found upon careful screening.

6. The value of relative distance between two points in the biplot will be calculated using the following formula.

$$D\left(A‒B\right)=\sqrt{{\left(a1\;‒\;b1\right)}^{2}+{\left(a2-b2\right)}^{2}}$$

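### One SAQ score above the threshold, with no untreated comparison, cannot show that a drug is 'effective' for a patient; indication statements should rest on a paired A-only versus B-only contrast

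*Protocol article*

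**What the plan says.** The protocol article's Assignment of interventions section gives every patient an active drug in both periods: "Treatment A: QSYQ dripping pills + TXL placebo + routine medication" and "Treatment B: TXL capsules + QSYQ placebo + routine medication", in one order or the other. The Routine medication section adds that "Routine medications will include aspirin, angiotensin-converting enzyme inhibitors or angiotensin receptor blockers, β-receptor blockers, statins and nitrates". The only phase without an active drug is the washout, when "patients in both groups will receive QSYQ placebo and TXL placebo plus routine medication for 10 days". Under Measurement tools and time of data capture, the SAQ and Likert scores serve to "collect PROs immediately following the first treatment period and the crossover treatment period". No measurement is stated for the washout.

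Under Efficacy assessment tools, item 4, "Treatment interventions will be defined as either effective or ineffective", and this is done "by comparison of the patient’s personal SAQ score with the calculated MCID value". Item 5 combines the two pass/fail results into Group 1 (both effective), Group 2 (A only), Group 3 (B only) and Group 4 (neither). Tables 1 and 2 tabulate these groups by symptom combination. Correspondence analysis, step 5, takes the closest symptom-outcome pair in the biplot as the strongest association and adds: "The characteristic indications for which the patent drug is most effective will be found upon careful screening".

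**The concern.** Each patient takes each drug once, and the rule has no control term. A pass may come from the drug, the background antianginal treatment, spontaneous fluctuation, placebo response or measurement noise, and nothing in the rule tells these apart. The printed label, however, is a statement about the drug in that patient, and these labels are the data for the main analysis.

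The trial is meant to name the indications for which each drug works best. A symptom combination lying near Group 1 could be taken as an indication when it shows only that those patients passed twice. A combination lying near Group 2 could be taken as favouring drug A although two identical drugs also put patients there by chance. No reference distribution or test is stated against which closeness is judged.

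**Working it through.** The plan gives no figure for the expected size of the four groups, so there is none to reproduce. The sample size calculation does not enter this point.

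**Inputs from the article.** 40 patients per symptom combination, 20 per sequence, and 20% dropout (Sample size calculation), so 40 × 0.80 = 32 completers. A pilot figure of 2 ± 2.5 for SAQ change (same section). Threshold: MCID = √(SEM0² + SEM1²), with SEM = SD × √(1 − r) (Efficacy assessment tools).

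**Assumptions, because the article does not give them.** Pass probability p per period, within-patient correlation ρ, reliability r of 0.7 to 0.9, and equal SD in the two Likert groups. For raw scores: a 0–100 scale, mean 50 to 70, SD 15 to 20.

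**1. Identical drugs, change-score reading.** Take a bivariate normal score with the same p in both periods and k = Φ⁻¹(p). Then Group 1 = Φ₂(k, k; ρ), Group 2 = Group 3 = p − Group 1, and Group 4 = 1 − 2p + Group 1.

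| p | ρ | Group 1 | Groups 2 and 3, each | Group 4 |
|---|---|---|---|---|
| 0.3 | 0.3 | 12.8% | 17.2% | 52.8% |
| 0.3 | 0.7 | 19.1% | 10.9% | 59.1% |
| 0.5 | 0.3 | 29.8% | 20.2% | 29.8% |
| 0.5 | 0.5 | 33.3% | 16.7% | 33.3% |
| 0.5 | 0.7 | 37.3% | 12.7% | 37.3% |
| 0.7 | 0.3 | 52.8% | 17.2% | 12.8% |
| 0.7 | 0.7 | 59.1% | 10.9% | 19.1% |

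So each of Groups 2 and 3 holds 11 to 20% with no difference between the drugs. At p = ρ = 0.5 that is 0.167 × 32 ≈ 5 patients per combination.

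**2. How easily the threshold is passed on that reading.** With SD 2.5, MCID = √2 × 2.5 × √(1 − r), which is 1.94 at r = 0.7 and 1.12 at r = 0.9. Patients with zero mean change pass with probability 1 − Φ(1.94/2.5) = 22% and 1 − Φ(1.12/2.5) = 33%. With a mean change of 2 from any cause, 51% and 64% pass.

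**3. Raw-score reading, as printed.** The lowest pass rate over the assumed ranges is at mean 50, SD 20, r = 0.7: MCID = √2 × 20 × √0.3 = 15.5, and the pass rate is Φ((50 − 15.5)/20) ≈ 96%. Over the rest of the range it reaches nearly 100%. Groups 2 and 3 are then almost empty and nearly everyone is in Group 1.

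**4. Chance gaps between combinations.** In simulation with identical drugs, p = ρ = 0.5 and 40 patients in each of four combinations, the largest absolute difference between A-only and B-only counts averaged 5.3 patients. It was at least 5 in 62% of trials.

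**5. Precision of the paired contrast.** At p = ρ = 0.5 the discordant share is 2 × 0.167 = 0.333. The standard error of A-only minus B-only is √(0.333/32) = 0.102, so the 95% margin is 1.96 × 0.102 = ±20 points. With all 40 patients it is 1.96 × √(0.333/40) = ±18 points.

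**6. The contrast fails on the groups as printed.** Items 5.b.ii and 5.c.ii place B-then-A patients who pass on B and fail on A in Group 2, and the reverse in Group 3. This contradicts the headings of both groups. Suppose pass rates of 70% on A and 50% on B, ρ = 0.5, no period effect and balanced sequences. The true shares are 27.8% A-only and 7.8% B-only. As printed, each group gets (27.8 + 7.8)/2 = 17.8%, a difference of zero. Conversely, take identical drugs whose pass rate rises from 50% in period 1 to 70% in period 2. Printed Groups 2 and 3 then hold 7.8% and 27.8%, about 12 and 44 of 160, whereas correct labels give 17.8% each.

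**The case against.** The aim is comparative and exploratory, both drugs are in common use, and 'effective' is an operational label. Correspondence analysis displays departures from the average profile, so improvement shared by all symptom combinations would not pull any of them towards Group 1; only a course that differs between combinations would. A paired, order-stratified interval is also a detail often left to an analysis plan.

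Much of this stands, and it limits the point. Four stronger readings are tempting, and the article does not support them:

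- That Groups 1 and 4 merely reflect natural course and routine medication. A real drug effect also enters them; the causes cannot be separated.
- That Groups 2 and 3 must fill up with identical drugs. This needs a change-score reading. The Sample size calculation speaks of changes, but the rule as printed compares the score itself, and the groups could then be nearly empty.
- That the lack of a placebo period biases the comparison of A with B. With correct labels and balanced sequences, identical drugs give equal expected A-only and B-only shares.
- That the plan says closeness to Group 1 or 4 makes an indication. It does not say so; it also does not exclude those groups from the screening step.

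The objection does not remove the core. The rule is printed in full rather than deferred, and the step that turns groups into indications has no stated chance reference. A comparative aim does not need an absolute label.

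**Conclusion.** The concern holds in limited form. The design cannot attribute a single pass to a drug, so the per-patient label 'effective' is unsupported, as is any indication drawn from closeness in the biplot alone. The design can support a within-patient comparison of the two drugs.

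The size depends on quantities that the article does not give. On a change-score reading with p and ρ each between 0.3 and 0.7, chance alone puts 11 to 20% of patients in each of Groups 2 and 3. On the raw-score reading, with the assumed mean and SD, about 96 to 100% pass and Group 1 says almost nothing about either drug. The attribution problem exists under both readings. It should be corrected, but it does not invalidate the randomised comparison.

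**What to change.** 1. Reconcile items 5.b.ii and 5.c.ii with their group headings, so that Group 2 means passed on A only and Group 3 passed on B only in both sequences. The contrast below is meaningless until this is done.
2. State whether the rule applies to the SAQ score or to its change.
3. Rename the groups: responded on both, on A only, on B only, on neither.
4. Base each drug-specific indication statement on the A-only minus B-only difference within each symptom combination, with a paired (McNemar-type) confidence interval stratified by treatment order.
5. Keep Groups 1 and 4 and the correspondence plot as description.
6. State that the trial compares the two drugs and does not show that either is effective.

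The cost is wording and one small table, with no new arm, visit or patient. The downside is that absolute claims of effectiveness are given up, and the wide intervals per combination will be visible.

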### Sample size calculation

Sample size estimation is based on the results of a pilot study that showed the difference in changes in Seattle Angina Questionnaire (SAQ) scores of 2 ± 2.5 between the group receiving QSYQ dripping pills and the group taking TXL capsules. Assuming a two-sided *P*-value of 0.05, 90% power and calculating for a dropout rate of 20%, one would need to have approximately 160 patients with 80 in each treatment group. We used the PAST software program to calculate these statistics (http://folk.uio.no/ohammer/past/) [10]. Therefore, we plan to recruit 40 patients for each of the four symptom combinations, from among whom 20 will be assigned to treatment arm A (QSYQ) and 20 to treatment arm B (TXL). In all, 160 patients will be recruited.

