#### *Baseline assessment*

General information about the patient’s gender, age and heart function will be collected and assessed after eligibility screening to ensure balanced baseline values.

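### The responder rule compares a raw end-of-period SAQ score with an MCID that the article defines as a change, and the stated SAQ timing names no pre-treatment measurement

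*Protocol article*

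**What the plan says.** The rule that turns each patient into a success or failure is in the protocol article under Efficacy assessment tools. Step 4.a reads "Treatment A will be defined as effective if a patient receiving it has a SAQ score greater than the MCID1 score", and step 4.b has the same form for treatment B. Step 5 sorts patients into Groups 1 to 4 by two such comparisons, for example "the first SAQ score > MCID1 and the second SAQ score > MCID4". All eight conditions in step 5 use the SAQ score. Nowhere in steps 1 to 5 is a patient's own earlier value subtracted.

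The Background section on MCIDs describes the MCID as reflecting "the smallest change in the PRO evaluations of a clinical intervention that is meaningful to the patient". The Sample size calculation is likewise built on a "difference in changes in Seattle Angina Questionnaire (SAQ) scores of 2 ± 2.5".

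On timing, Measurement tools and time of data capture places the SAQ and the Likert scale "immediately following the first treatment period and the crossover treatment period", and the MCIDs "at these two time points will be calculated for efficacy evaluation and comparison". Under Baseline assessment, "gender, age and heart function will be collected and assessed after eligibility screening"; the SAQ is not named there.

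**The concern.** A threshold for change is being applied to a level. The MCID formula yields a fraction of the between-patient SD, whereas a raw SAQ score may lie several SD above zero. A patient can therefore clear the threshold without having improved at all.

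Groups 1 to 4 are the only columns of Tables 1 and 2, and those tables are the only input to the correspondence analysis. If most patients fall into Group 1 whatever the drugs do, there is little left with which to identify the best indication for each drug, which is the stated aim.

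The stated timing cannot repair this. With scores only at the end of each period, a within-period change cannot be computed. The second period in particular has no starting value after the 10-day washout, so any benefit that did persist from the first drug could not be told apart from the effect of the second.

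**Working it through.** The article states no expected share of responders, so there is no figure of its own to reproduce on this point. The planned total of 160 is not used; only the 40 patients per symptom combination are.

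**Threshold.** From steps 1 to 3:

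- M0 and M1 are deviations of SAQ scores from their Likert-subgroup mean, so √(ΣM²/(n−1)) is the subgroup SD.
- SEM = SD × √(1−r), and MCID = √(SEM0² + SEM1²).
- With equal SDs in the two subgroups (assumption), MCID = SD × √(2(1−r)).
- The article gives no value for r. Assuming 0.7, 0.8 and 0.9: √0.6 = 0.77, √0.4 = 0.63 and √0.2 = 0.45 SD.

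**Share called effective on one drug under the literal rule.** For a normally distributed raw score (assumption), P(score > MCID) = Φ(mean/SD − √(2(1−r))). The article gives no SAQ mean or raw-score SD, so the ratio is varied:

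| r | MCID in SD | mean/SD = 1.6 | 2 | 2.5 | 3 | 4 |
|---|---|---|---|---|---|---|
| 0.7 | 0.77 | 80% | 89.0% | 95.8% | 98.7% | 99.94% |
| 0.8 | 0.63 | 83% | 91.4% | 96.9% | 99.1% | 99.96% |
| 0.9 | 0.45 | 88% | 94.0% | 98.0% | 99.5% | 99.98% |

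The column for 1.6 is a deliberately unfavourable case (mean 40, SD 25; 40/25 = 1.6).

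**Share in Group 1 (effective on both).** If the two periods were independent, this is the square of the share for one drug:

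- mean/SD = 2: 0.8898² = 79.2%, 0.9143² = 83.6%, 0.9398² = 88.3%.
- mean/SD = 3: 97.4%, 98.2%, 98.9%.

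Positive correlation between a patient's two scores raises these shares. Of the 40 patients planned per symptom combination, those left for Groups 2, 3 and 4 together number, under independence:

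- at 2 SD: 40 × (1−0.8832) = 4.7 to 40 × (1−0.7917) = 8.3;
- at 3 SD: 40 × (1−0.9893) = 0.4 to 40 × (1−0.9741) = 1.0.

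**Sensitivity to a drug effect.** At r = 0.8, a drug that raises the mean by half an SD, from 2.5 to 3 SD above zero, moves the share effective from 96.9% to 99.1%, or 2.2 percentage points.

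**Illustration by simulation.** This took 160 crossover patients, an assumed 0–100 scale, pre-treatment mean 55, SD 18 and r = 0.8, with no period or carry-over effect. The whole-sample SD stood in for both subgroup SDs, and the same threshold was used for both rules.

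| True effect | Rule | Group 1 | Group 2 (A only) | Group 3 (B only) | Group 4 |
|---|---|---|---|---|---|
| none | score | 98.7% | 0.5% | 0.5% | 0.3% |
| none | change | 2.6% | 13.3% | 13.2% | 70.9% |
| A +10, B 0 | score | 99.2% | 0.7% | 0.0% | 0.1% |
| A +10, B 0 | change | 7.4% | 38.4% | 8.6% | 45.6% |

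In this setting the score rule gives almost the same table whether or not A works, while the change rule shows the difference.

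**The case against.** The strongest reply is that the SAQ score in steps 4 and 5 is shorthand for a change. The Background speaks of changes in PROs, the sample size uses changes, and the signed Likert bands (0 to +1, +2 to +3) look like ratings of improvement. On that reading the predicted crowding into Group 1 does not arise. This is plausible, but it leaves a rule whose wording is wrong throughout and a timing statement that cannot supply the change intended.

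A reader might also infer that the trial collects no baseline SAQ at all. The documents do not establish that. The timing statement does not say that its two points are the only ones. The baseline list is evidently incomplete, since the baseline balance test uses living status and education level, which it omits. The flowchart and the figure for the M value are not shown, and an article condenses the full protocol. What stands is narrower: the article states a timing, bases the MCIDs on it, and names no earlier SAQ.

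Two further inferences should be resisted. The figure of 2.5 in the sample size section should not be used to express the MCID in points: it belongs to changes, and the formula as written uses raw scores. Nor do the documents show that the placebo washout fails to remove carry-over; the point is only that no stated measurement would reveal it.

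**Conclusion.** The point holds as an inconsistency in the rule that generates every efficacy result: the threshold is defined as a change, the quantity compared with it is a level, and the stated measurements do not allow a change to be formed. The rule as written has to be corrected before the first patient is treated, because a missing baseline cannot be recovered later.

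The size of the consequence is conditional on the literal reading, equal subgroup SDs, approximate normality, r between 0.7 and 0.9, and an assumed ratio of mean to SD. It would go too far to say that nearly every patient will be effective on both drugs and that the trial cannot distinguish them. At a mean 2 SD above zero, up to about a fifth of patients could still fall outside Group 1, and with low, widely spread scores the share per drug drops to 80–88%. Across the whole range examined, however, most patients pass on each drug largely regardless of its effect.

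**What to change.** - In Efficacy assessment tools, replace the SAQ score by the SAQ change over that treatment period (end of period minus the value before that period) in step 1 (X0 and X1), in step 4 and in all conditions of step 5. State that r is then the reliability of the same quantity, the change.
- In Measurement tools and time of data capture, state that the SAQ is also collected before the first treatment period and at the end of washout, before the second. Add it to Baseline assessment.

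The cost is the rewording and up to two extra administrations of a questionnaire already in use, or none if the full protocol already has them. The article does not show whether patients attend at the end of washout, so that time point may need a visit or a remote completion.
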